### Study setting

The trial will be conducted according to the International Conference of Harmonization Good Clinical Practice Guidelines and adheres to the Declaration of Helsinki. IRB approval will be obtained in all participating centers. All participants must give their voluntary and written informed consent before any study related procedures could take place. Individuals who meet the entry criteria and complete the baseline visit will be enrolled in one of the five participating University Medical Centers: Groningen and Nijmegen, (the Netherlands), Cologne (Germany), Leuven (Belgium) and Barcelona (Spain).

### Patient selection

Detailed inclusion criteria are given in Table 1, of which the most important are:Female patients, pre-menopausalAnti Mullerian Hormone (AMH) level > 0.3 (a lower level indicates upcoming menopause)Age 18–45 years (inclusive)PLD with a very large liver for age, based on the upper 10% of volumes in our PLD registry (n = 1600) [27].One historical MRI or CT scan, performed 1–5 years before baseline, available to calculate liver growth before start of the studyOngoing liver growth, confirmed using a historical scan (a) obtained in routine clinical care and the scan at screening (b) with the liver volume in ml from scan b–a > 0.Use of a somatostatin analogue (only proven effective therapy currently available) or reason not to use such drug (e.g. not tolerated, ineffective, not available)

**Table 1 Tab1:** Overview of in- and exclusion criteria for the AGAINST-PLD study

Inclusion criteria	
Female	
Diagnosis of PLD (presence of > 10 cysts)	
Age 18–45 (inclusive) years	
Very large liver for age:	
18–30 y hTLV > 2.0 L/m	
30–35 y hTLV > 2.2 L/m	
25–40 y hTLV > 2.5 L/m	
40–45 y hTLV > 3.0 L/m	
1 historical MRI or CT scan of the liver available, made 5-1 y before baseline	
Ongoing liver growth, confirmed using the historical scan and MRI scan at screening	
Use of somatostatin analogues OR a reason not to use them (e.g. tried in de past but stopped because of side effects, not effective, no acces, patient does not want to)	
Voluntary written informed consent	

Exclusion criteria	
Post menopausal status or (vasomotor) symptoms indicating upcoming menopause	
AMH < 0.03 ng/ml at screening	
Active desire to have children, pregnancy or breast-feeding	
Contra-indications for leuprorelin, such as cardiovascular disease or osteoporosis	
Liver transplantation expected within 1.5 years	
Use of oral estrogen or progesterone containing medication	
Contra-indications for MRI	
Chronic use of immunosupressive agents	
Severe hypertension (systolic pressure ≥ 160 and/or diastolic pressure ≥ 100 mmHg)	
Clinically significant uncontrolled medical condition that, in the opinion of the investigator, would put the safety of the patient at risk though participation, or which would affect efficacy or safety analysis, such as, but not limited to, recurrent cholangitis, recurrent ascites, hepato-venous outflow obstruction, (history of) depression	
Participation in other interventional studies at the same time	

Exclusion criteria related to the historical MRI/CT scan	
Start or stop of liver volume reducing therapy (medication e.g. somatostain analogues or surgical interventions) between the historical scan and screening	
Historical scan is performed < 3 months after start or stop of volume reducing therapy (either a somatostatin analogue or surgical treatments)	

Most important exclusion criteria are:Symptoms of (upcoming) menopause, e.g. hot flushesActive desire to have children during study periodUse of exogenous estrogen and/or progesteroneContra-indication for leuprorelin

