### Concomitant medication

For massive PLD, somatostatin analogues are currently the only evidence-based treatment. Therefore, somatostatin analogues should be used, tried, or have been considered before inclusion in the AGAINST-PLD trial. Patients are thus allowed to use a somatostatin analogue during the trial (see inclusion criteria, Table 1). During the study, start or stop of somatostatin analogues as well as surgical procedures to reduce liver volume should be avoided unless there are important reasons to do so, because this could interfere with the assessment of the primary outcome, liver growth.

Use of estrogen- and or progesterone containing medication is not allowed during the trial period, because it could interfere with the effect of the study treatment. Blood pressure treatment is targeted below 130/80 mmHg with RAAS-inhibitors as the first-choice agents. Calcium vitamin D (500 mg/800 IE) will be prescribed to all patients in the study to prevent osteoporosis.

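### Eligibility thresholds in Patient selection and Table 1 contradict each other: overlapping age bands for liver volume, two AMH cut-offs, and a minor mismatch in the hormone exclusion

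*Protocol article*

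**What the plan says.** Patient selection introduces its list with the words "Detailed inclusion criteria are given in Table 1, of which the most important are". The text list is therefore offered as a selection from Table 1, and the two should agree.

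- **Liver volume for age (Table 1).** Four rows: "18–30 y hTLV > 2.0 L/m", "30–35 y hTLV > 2.2 L/m", "25–40 y hTLV > 2.5 L/m" and "40–45 y hTLV > 3.0 L/m". The text describes the same criterion as the top 10% of volumes for age in the investigators' registry.
- **AMH.** The text list makes AMH above 0.3 an inclusion criterion, gives no unit, and explains that lower values point to approaching menopause. Table 1 has no AMH inclusion criterion; its exclusion list has "AMH < 0.03 ng/ml at screening".
- **Hormonal medication.** Table 1 excludes "Use of oral estrogen or progesterone containing medication". The short list of main exclusions after the table bars exogenous estrogen and/or progesterone and names no route. Under Concomitant medication, "Use of estrogen- and or progesterone containing medication is not allowed during the trial period", again without a route.

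**The concern.** These are yes/no rules that decide who is randomized, and five centres in four countries will apply them to 36 patients. Where two stated values conflict, two centres can follow the document faithfully and reach opposite decisions about the same woman.

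Two things are at stake. The first is the definition of the population: pre-menopausal women whose livers are very large for their age. The second is the per-protocol sensitivity analysis announced under Statistics. If eligibility violations count in defining that set, as is usual, a woman can be a violator under one list and compliant under the other.

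**Working it through.** The check is a comparison of stated thresholds. The plan gives no derived figure to reproduce on this point.

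**1. Age bands.** Each whole-year age from 18 to 45 (28 ages) was assigned to every Table 1 row that contains it, end points included.

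| Age (years) | Thresholds that apply (L/m) | Gap, lowest to highest |
|---|---|---|
| 18–24 | 2.0 | none |
| 25–29 | 2.0 and 2.5 | 0.5 |
| 30 | 2.0, 2.2 and 2.5 | 0.5 |
| 31–35 | 2.2 and 2.5 | 0.3 |
| 36–39 | 2.5 | none |
| 40 | 2.5 and 3.0 | 0.5 |
| 41–45 | 3.0 | none |

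Ages with more than one threshold: 5 (25–29) + 1 (30) + 5 (31–35) + 1 (40) = 12 of 28.

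Worked cases:
- Age 28, hTLV 2.3 L/m: 2.3 > 2.0, so she meets the 18–30 row; 2.3 < 2.5, so she fails the 25–40 row.
- Age 33, hTLV 2.3 L/m: 2.3 > 2.2, so she meets the 30–35 row; 2.3 < 2.5, so she fails the 25–40 row.
- Age 40, hTLV 2.7 L/m: 2.7 > 2.5, so she meets the 25–40 row; 2.7 < 3.0, so she fails the 40–45 row.

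No tie-break rule is stated. If the strictest row governs, the 30–35 row never has any effect, because every age in it also falls under > 2.5. If the most lenient row governs, the 25–40 row has no effect below age 36. Either way, part of the table as printed is idle.

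Suppose the lower limit of the third row is a slip and that row starts where the second ends. The shared end points 30, 35 and 40 would still each belong to two rows.

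**2. AMH.** The text admits AMH > 0.3 (unit not stated). Table 1 excludes AMH < 0.03 ng/ml, so 0.03 ng/ml and above is not excluded.
- If both are in ng/ml, the ratio is 0.3 / 0.03 = 10. Values from 0.03 up to and including 0.3 fail the text and pass the table. A woman with 0.1 ng/ml is an example.
- For the two cut-offs to coincide, one unit of the text's scale would have to equal 0.03 / 0.3 = 0.1 ng/ml. The document names no such unit.

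**3. Hormonal medication.** A user of a non-oral product is not excluded by Table 1, is excluded by the text list, and could not continue the product under Concomitant medication. Two of the three statements agree; only the word oral in Table 1 is narrower.

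**4. Is any of this settled elsewhere?** Randomization assigns age 40 to the upper stratum (< 40 versus ≥ 40), but that concerns stratification, not the volume threshold. No other section resolves the age bands or the AMH cut-off.

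**The case against.** **These look like typing slips in a condensed article.** The rows run in order and the thresholds rise, so a wrong digit in the third row is likely, and shared end points are common shorthand. The full protocol is not shown, and sites may never work from this table. That much stands, and the document does not show that anyone was wrongly enrolled. But condensing explains what is left out, not two conflicting stated values. For AMH, nothing in the document shows which figure is intended.

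**A patient must meet every inclusion criterion and no exclusion criterion, so the stricter AMH rule simply governs.** That is logically possible. It would leave the table's cut-off without function if the units match, and the text names Table 1 as the detailed list, yet the 0.3 criterion is not in it.

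**The tenfold AMH gap is conditional.** This stands: it assumes ng/ml in both places. A missing unit on a decision threshold is itself a defect.

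**The hormone mismatch matters little.** This also stands. A reader might infer that non-oral hormone users would be admitted and remain exposed. The text's main exclusions and Concomitant medication both bar these products by any route, so this is a wording point only.

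**A reader might infer a loss of power.** The argument would be that women with low AMH enter, do not grow, and shrink the contrast behind the sample size. The documents do not support it:
- They give no share of women with AMH between the two cut-offs.
- Every patient must show ongoing growth between the historical and screening scans.
- Symptoms of approaching menopause are a separate exclusion.
- The background section on female hormones says that volume sometimes falls after menopause; it does not say this of women approaching it.

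Any power figure would rest on an invented share. One based on 18 per arm would also ignore the 20% drop-out already built into the 36.

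**Conclusion.** The contradictions in the age bands and the AMH cut-off are real, stand in the current text, and are not resolved anywhere in the article. The age-band conflict covers 12 of 28 whole-year ages, with gaps of 0.3 to 0.5 L/m. The AMH conflict covers 0.03 to 0.3 ng/ml, on the assumption that the text value is in ng/ml. The hormone item is a minor mismatch of wording.

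The consequence is limited to an unclear target population (top 10% of liver volume for age, pre-menopausal) and unclear eligibility-violation status for the per-protocol analysis, if that set depends on eligibility. The sample size calculation is not affected. Because the values decide who may be randomized, reconciling them is more than a clerical correction, even if each began as a slip.

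**What to change.** The sponsor should reconcile the running text and Table 1 to one set of rules and confirm which values are intended; this review does not choose between them.

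- **Age bands:** non-overlapping rows, with explicit inclusive or exclusive signs at each boundary.
- **AMH:** one cut-off with its unit, stated the same way in text and table.
- **Hormonal medication:** one wording on route, used in Table 1, in the text exclusions and under Concomitant medication.

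The same rules should then be checked against the full protocol and mirrored in the eligibility check used before randomization. If patients have already been screened, record which rule was applied to each, so that violation status can be assigned consistently. The cost is a correction to the text and table and an edit check. No extra patients or visits are needed.

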### Randomization

Participants will be randomized 1:1 between direct and delayed start (after 18 months) of treatment using an online Interactive Response System (IXRS) tool, stratified for somatostatin analogue use (yes/no) and age (< 40 and ≥ 40 years).

### Intervention

Leuprorelin is a synthetical analogue of GnRH and strongly stimulates the pituitary resulting in desensitization. Thus, the production of luteinizing hormone (LH) and follicle stimulating hormone (FSH) by the pituitary stops, which leads to cessation of the production of estrogen and progesterone by the ovaries.

Leuprorelin will be started using monthly injections of 3.75 mg, and if tolerated after 3 months, treatment regimen will be switched to 3-monthly injections of 11.25 mg. Depending on patients’ preferences, participants will be trained to self-administer the injections at home or injections will be administered by study personnel.

### Concomitant medication

For massive PLD, somatostatin analogues are currently the only evidence-based treatment. Therefore, somatostatin analogues should be used, tried, or have been considered before inclusion in the AGAINST-PLD trial. Patients are thus allowed to use a somatostatin analogue during the trial (see inclusion criteria, Table 1). During the study, start or stop of somatostatin analogues as well as surgical procedures to reduce liver volume should be avoided unless there are important reasons to do so, because this could interfere with the assessment of the primary outcome, liver growth.

Use of estrogen- and or progesterone containing medication is not allowed during the trial period, because it could interfere with the effect of the study treatment. Blood pressure treatment is targeted below 130/80 mmHg with RAAS-inhibitors as the first-choice agents. Calcium vitamin D (500 mg/800 IE) will be prescribed to all patients in the study to prevent osteoporosis.

### Outcome parameters

#### Primary outcome

Liver growth (%/y), calculated over the first 18 months of the trial and compared between the direct start group (on treatment) and delayed start group (on standard of care), b–e versus b–c, Fig. 3.

#### Secondary outcomes

Change in PLD disease severity, assessed by the validated PLD-Q questionnaire, calculated over the first 18 months of the trial and compared between the direct start group (on treatment) and delayed start group (on standard of care).Liver growth rates within individuals compared before treatment and during treatment. In the direct start group, historical growth rates (Fig. 3a, b) will be compared with growth rate during 18 months of treatment (b–e) and in the delayed start group, growth rates during the first 18 months of the trial (untreated, b–c) will be compared with the last 18 months of the trial (treated, c–d).The incidence of (serious) adverse events, compared between the direct and delayed start group in the first 18 months of treatment.

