### MRI scans

Liver and kidney volumes (the latter in ADPKD patients only) will be measured using an MRI scan at screening, 6, 18, 24 and 36 months. MRI scans will be performed using a standardized protocol, including a coronal T2-weighted single-shot fast gradient spin-echo sequence with fat-saturation with a slice thickness of 3 mm which is the primary sequence to determine liver volumes. In addition, a transversal T2-weighted single shot fast gradient spin-echo sequence with fat suppression and a coronal T1-DIXON-VIBE spoiled gradient echo sequence will be obtained. After pseudonymization, MRI scans will be sent to the central reading facility, where images will be analyzed blinded for patient, time and treatment by trained observers using an automated MRI program [30]. To ensure that valid MR images are obtained, quality control will be performed within 72 h by trained personnel. In case a scan is rejected, it will be repeated.

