### Statistics

#### Statistical analysis

Analyses are performed after completion of the study. For the primary outcome, liver growth during the first 18 months of the trial compared between direct and delayed starters, an unpaired t-test will be used. In case of missing data, last information will be used adjusted for the duration of follow up. For questionnaires, the delta in scores during the first 18 months of the trial will be compared between direct and delayed starters. To compare liver growth within individuals before and during treatment, a paired t-test will be used. Adverse events will be categorized and the number of adverse events per category will be compared between direct and delayed starters using an unpaired t-test.

For all primary and secondary analyses, we will perform pre-defined sensitivity analysis to adjust for age, disease type (ADPKD vs. ADPLD), total liver volume at baseline, total kidney volume at baseline, use of somatostatin analogues, and test differences in treatment effects among these variables (interaction). In a sensitivity analysis we will test for differences in the outcome variables between the first 18 months of the trial and the second 18 months of the trial in the direct start group, using a breakpoint analysis. All analyses will be performed based on an intention to treat principle. As a sensitivity analysis, we will perform a per-protocol analysis.

In an additional analysis we will explore whether liver growth is linear and whether the liver growth rate during treatment is different in the first 6 months of treatment compared to the 12 months thereafter, using a multiple mixed model.

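### In the direct-start arm, the before/during comparison may span a change from CT to MRI in the 'before' period only, and the analysis as described does not allow for it

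*Protocol article*

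**What the plan says.** Under Secondary outcomes, the within-person comparison has two halves. In the direct-start arm, "historical growth rates (Fig. 3a, b) will be compared with growth rate during 18 months of treatment (b–e"), that is, scans a to b against scans b to e. In the delayed-start arm, "growth rates during the first 18 months of the trial (untreated, b–c) will be compared with the last 18 months of the trial (treated, c–d").

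The scans come from different sources. Table 1 (Patient selection) requires "1 historical MRI or CT scan of the liver available, made 5-1 y before baseline". The list above that table says ongoing growth is "confirmed using a historical scan (a) obtained in routine clinical care and the scan at screening (b"). For the trial's own scans, from screening to month 36, the MRI scans section says "MRI scans will be performed using a standardized protocol", with quality control and repetition of rejected scans.

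On analysis, the Statistical analysis section says "To compare liver growth within individuals before and during treatment, a paired t-test will be used". It adds that "we will perform pre-defined sensitivity analysis to adjust for age, disease type (ADPKD vs. ADPLD), total liver volume at baseline", followed by kidney volume and somatostatin analogue use. Scan modality is not on that list. The exclusions in Table 1 that relate to the historical scan concern starting or stopping volume-reducing therapy, not the type of scan.

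**The concern.** A paired comparison removes a measurement offset only if the offset is the same at every scan it uses. Here it may not be. Scan b is shared by both periods and is a study MRI, as is scan e, while scan a may be a CT. A constant difference between CT and study MRI therefore enters the change from a to b in full and the change from b to e not at all. If CT reads low against study MRI, historical growth looks too fast and treatment appears to slow it. If CT reads high, a real slowing is hidden. Pairing within a woman does not help, because the change of instrument happens within the woman.

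The delayed-start half uses study MRI throughout. The two halves of one secondary outcome could thus disagree for a technical reason. The article gives the within-person comparison as one of the reasons for the delayed-start design (Study design; Discussion), so its interpretation matters.

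**Working it through.** **Inputs from the article.** Untreated growth is 5.8% per 18 months with SD 2.8%, and the SD is doubled for planning (Sample size calculation). The aim is to stop growth fully. The interval T from a to b is 1–5 years (Table 1). Randomisation is 1:1 with 36 women, so about 18 per arm. No sample size or effect is stated for this within-person comparison, so there is no figure of the plan to reproduce. The planned effect on the annual scale is 5.8/1.5 = 3.87 %/y.

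**Inputs not in the article (assumed).** Offset d = 1–5% of liver volume, CT share 50%, T uniform over 1–5 years, scan error SD 1% or 2% per scan.

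**Shift for one woman with a CT.** If scan a reads d% low, the 'before' rate rises by about d/T and the 'during' rate by 0. For d = 3%:

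- T = 1 y: 3.0 %/y
- T = 2 y: 1.5 %/y
- T = 5 y: 0.6 %/y

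**Shift of the group mean, which is what the t-test tests.** With T uniform on 1–5, the mean of 1/T is ln(5)/4 = 0.402. Expected shift = d × 0.402 × CT share.

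| d | Shift, half CT | Share of 3.87 %/y |
|---|---|---|
| 1% | 0.20 %/y | 5% |
| 2% | 0.40 %/y | 10% |
| 3% | 0.60 %/y | 16% |
| 5% | 1.01 %/y | 26% |

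If every historical scan were a CT, the shifts would double (3%: 1.21 %/y, 31%). If CT reads high, the sign reverses.

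**Chance of falsely declaring a fall in growth.** Paired t-test simulated with 18 women, no drug effect, d = 3%, half CT, and no selection on past growth. The nominal rate in this direction is 2.5%. The result depends on how far a woman's true growth rate differs between her two periods:

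| True growth in the two periods | Scan error SD 1% | Scan error SD 2% |
|---|---|---|
| Identical | about 35% | about 13% |
| Independent, SD 2.8/1.5 = 1.87 %/y | about 12% | about 9% |
| Independent, doubled SD 5.6/1.5 = 3.73 %/y | about 6% | about 6% |

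With d = 0 the rate is about 2.5% in every case, so the excess comes from the offset. The mean shift is the same in all rows. It is therefore the steadier measure of size.

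**The case against.** The strongest objection is that the driving quantity is unknown. The article neither gives nor implies a systematic CT–MRI volume difference, its sign, or how many historical scans will be CT. With no offset there is no bias. That stands, and it is why the figures above are an illustration and not an estimate.

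A second objection is that the handling of historical scans may sit in the full protocol, an imaging manual or the SAP. That is possible. But the article itself fixes the permitted modalities, the contrast, the test and the adjustment list, and those four together leave the comparison open to an offset. Reading all historical scans centrally would not by itself remove a difference between modalities.

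Third, the scope is narrow: one arm of one secondary outcome. That stands too.

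Three stronger readings are tempting and are not supported:

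- A reader might infer that the bias could reach most of the planned effect, since 3.0/3.87 = 78%. That is a single woman with a CT taken exactly one year earlier. The group mean in the same scenario moves by 16%.
- A reader might take 35% as the false-positive rate. It requires each woman's growth to be identical in both periods and scan error to be small. Otherwise the rate falls towards 6%.
- A reader might infer that the stated blinded reading fails for CTs, or that CTs are to be read with MRI software, because "images will be analyzed blinded for patient, time and treatment by trained observers using an automated MRI program". That sentence belongs to the section on the scheduled study MRIs and says nothing on how historical scans are read.

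**Conclusion.** The point holds as a limited one. The direct-start before/during comparison can absorb a CT–MRI volume difference into the apparent effect of leuprorelin, in either direction, and neither the paired t-test nor the listed adjustments would show it. Under the stated assumptions the group mean moves by about 0.2–1.0 %/y, or 5–26% of the planned effect. This rests on an assumed offset and CT share, and shrinks in proportion if either is smaller.

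The primary outcome (b–e against b–c) and the delayed-start comparison (b–c against c–d) use study MRI only and are untouched. The problem is also separate from the entry rule that volume must have risen between a and b: it arises with or without that rule.

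**What to change.** 1. Record the modality of scan a (CT or MRI) for every woman.
2. For the direct-start before/during comparison, pre-specify one further analysis: either restrict it to women whose historical scan is an MRI, or regress the paired difference on a CT indicator and report the estimate for MRI–MRI women.
3. Report it beside the pooled paired t-test, and interpret the pooled result as a drug effect only if the two agree.

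Which of the two analyses is labelled as the main one is a matter of judgement. What matters is that both are fixed in advance.

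The cost is wording and one recorded variable, with no extra scans or patients. The price is precision: an arm of about 18 loses an unknown number of women in the restricted analysis, so its interval will be wider. The fix is also partial. An MRI-only analysis leaves any difference between routine and study MRI in place, and it does not remove the selection on b − a > 0.

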## Methods and design

### Study design

The AGAINST-PLD study (A GnRH Agonist IN premenopausal women Study to Treat Polycystic Liver Disease) is a 3-year lasting, investigator driven, phase 2b randomized controlled trial. Participants will be randomized between direct start or delayed start (18 months later) of leuprorelin treatment (Figs. 2, 3). Patients randomized to delayed start will receive standard of care in the first 18 months of the trial. Therefore, in the first 18 months of the trial, we can distinguish between the effect of treatment and the natural course of disease by comparing both treatment arms. Using data obtained during the second 18 months of the trial, when all patients are subjected to active treatment, we can compare liver growth rates within individuals before start of treatment and during treatment and obtain more information about safety and tolerability.

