## Data collection and management

The study consists of one or two screening visits, nine hospital visits and one phone call. During short visits (3, 12, 15, 21 months), a small set of local laboratory measurements, vital signs, AEs and concomitant medication will be assessed. At larger visits (BL, 6, 18, 24 and 36 months) in addition MRI scans, extensive lab and questionnaires will be performed. DEXA scans are made at baseline, halfway and end of the study (Figs. 3, 4). Data will be entered in a web-based electronic case report form to ensure correct and timely data collection in a central database.

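### The adverse-event window, read literally, compares leuprorelin with leuprorelin, and the planned t-test on event counts does not match the stated incidence outcome

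*Protocol article*

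**What the plan says.** The Secondary outcomes section of the Protocol article has, as its third item, an incidence of adverse events, including serious ones. It is to be "compared between the direct and delayed start group in the first 18 months of treatment".

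The first item in that list, change in the PLD-Q score, has a different window. It is "calculated over the first 18 months of the trial and compared between the direct start group (on treatment) and delayed start group (on standard of" (the quote stops one word before its end), so the contrast between drug and control is spelled out.

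The Study design section fixes what each arm receives. "Patients randomized to delayed start will receive standard of care in the first 18 months of the trial". The second 18 months are the period "when all patients are subjected to active treatment".

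The Statistical analysis section says that events will be categorised and that "the number of adverse events per category will be compared between direct and delayed starters using an unpaired t-test". It gives no time window for this test.

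On collection, the Data collection and management section begins its list of short visits with "During short visits (3, 12, 15, 21 months" and says that at these "a small set of local laboratory measurements, vital signs, AEs and concomitant medication will be assessed". Larger visits fall at baseline and at 6, 18, 24 and 36 months.

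**The concern.** There are two separate problems.

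**The window.** Time on treatment starts at month 0 for direct starters and at month 18 for delayed starters. A comparison over the first 18 months of treatment therefore sets drug against drug. It can show whether the two on-drug periods look alike, but not what leuprorelin adds to standard of care. Adverse events are a named secondary objective, and the Discussion relies on an efficacy-safety balance, so the window has to be unambiguous.

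**The test.** The outcome is an incidence, but the analysis is of event counts. One patient with a recurring complaint can outweigh many patients who each have one event. Raw counts also fall when patients leave early, so an arm that loses patients can look safer because it was observed for less time.

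**Working it through.** The article states no power or sample size for adverse events, so there is no figure of the plan's own to reproduce on this point. The arm size of 18 is the planned 36 patients divided 1:1.

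**1. Window, by arm**

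| Reading | Direct start | Delayed start | Contrast |
|---|---|---|---|
| First 18 months of treatment | months 0-18, leuprorelin | months 18-36, leuprorelin | drug v drug |
| First 18 months of the trial | months 0-18, leuprorelin | months 0-18, standard of care | drug v control |

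The article uses the two terms distinctly elsewhere. In the within-individual outcome of the same section, 'of treatment' marks time on drug and 'of the trial' marks the delayed arm's untreated period. The exploratory comparison of the first 6 months with the next 12 also counts from the start of drug.

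**2. Scheduled visits under each reading**

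The nine hospital visits are baseline and months 3, 6, 12, 15, 18, 21, 24 and 36.

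- Literal reading: direct starters have 5 visits after starting drug (3, 6, 12, 15, 18). Delayed starters have 3 (21, 24, 36, which are 3, 6 and 18 months after their start). Each patient also has one phone call a month after the first injection.
- Trial reading: both arms have the same 5 visits.

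**3. Is the t-test's size wrong when follow-up is equal?**

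Per-patient counts were simulated with no true difference: 14 or 18 per arm, assumed means of 0.1 to 6 events, Poisson or negative binomial (dispersion 1 or 2), 100,000 runs each. At nominal 5%, the pooled test rejected in 1.6% to 5.1% of runs and the Welch test in 1.1% to 5.0%. There is no inflation. The test is conservative for rare categories.

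**4. Dominance by one patient (constructed data, 18 per arm)**

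- Direct: 13 patients with one event each, mean 13/18 = 0.72.
- Delayed: 6 patients affected, five with one event and one with 15, mean (5 + 15)/18 = 1.11.
- Patients affected, 13/18 v 6/18: Fisher p = 0.044, more in the direct arm.
- Counts: t-test p = 0.64, with the means in the opposite order.

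The means are equal when that patient has 8 events (5 + 8 = 13), so a reversal needs more than 8. Two events in that patient already move the t-test from p = 0.019 to p = 0.072.

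**5. Unequal follow-up**

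Assume equal true Poisson rates in both arms, 18 per arm, and 4 direct starters leaving early. Four of 36 is 11%, below the planned 20% drop-out. Month 4 lies just after the 3-month period in which drop-outs are replaced.

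Mean follow-up in the direct arm with departure at month 4: (14 × 18 + 4 × 4)/18 = 14.9 months against 18, a 17% fall in expected counts. At month 9: (14 × 18 + 4 × 9)/18 = 16 months, an 11% fall.

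| Rate per patient-year | Leave at month 4 | Leave at month 9 | No early leavers |
|---|---|---|---|
| 2 | 12% | 8% | 2.5% |
| 4 | 17% | 10% | 2.5% |

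Entries are the share of 200,000 simulated trials in which the pooled t-test finds significantly fewer events in the direct arm. The nominal value is 2.5%.

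**6. What the corrected comparison could show**

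Fisher power at 14 / 18 per arm, for assumed patient-level incidences: 80% v 10%, 0.97 / 0.996; 50% v 20%, 0.26 / 0.36; 30% v 10%, 0.14 / 0.20. Common effects would be detectable. For rarer ones the interval matters more than the p-value.

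**The case against.** The strongest reply is that 'treatment' is a slip for 'trial'. The article compares the two randomised groups, gives the delayed arm standard of care for 18 months, says that this period separates the drug's effect from the natural course, and collects adverse events in both arms from month 3. This is plausible. A reader might infer from the literal wording that the trial has no safety control, and the documents do not support that: the control exists. Other tolerability comparisons are also controlled. Questionnaire changes are compared over the first 18 months of the trial, and bone density is compared between arms after 18 months. A monitoring board meets regularly, and a formal interim analysis covers safety. What remains is that the text defining this outcome points to the other window, and nothing in the article corrects it.

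A reader might also call the t-test invalid. Step 3 does not support that. Nor is a gap from Fisher's test proof of a false positive. For 4/18 v 0/18 patients with one event each, the t-test gives p = 0.034 and Fisher p = 0.104, but Barnard's exact test gives 0.038 and Boschloo's 0.065. Much of the gap is Fisher's conservatism.

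Finally, the Statistical analysis section does adjust for length of follow-up when data are missing. That sentence follows the primary-outcome test and concerns using the last available information. Its reach to event counts is unclear, and full detail may sit in a document not shown. The t-test on event counts, however, is stated in the article itself.

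**Conclusion.** The point holds as an unresolved wording error in a secondary outcome together with an ill-suited test. It does not show that the design lacks a safety control.

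- **Window:** followed literally, the comparison is drug v drug with 5 v 3 scheduled visits after starting drug, and it cannot show leuprorelin's harms. This follows from the text alone. The visit imbalance disappears under the trial reading.
- **Test:** it does not match the stated incidence, is sensitive to one patient with recurrent events, and has no stated follow-up adjustment for events. With unequal drop-out, the false finding of greater safety rose from 2.5% to between 8% and 17% in the scenarios tried. Type I error is not inflated when follow-up is equal.

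The article gives no adverse-event rates. The rates, dispersions, incidences, recurrence pattern and drop-out times used here are all assumptions, and the percentages illustrate direction and order of size only.

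The window matters more, because it decides what is being compared.

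**What to change.** 1. In Secondary outcomes, set the window to the first 18 months of the trial, direct start on leuprorelin versus delayed start on standard of care, and repeat that window in Statistical analysis.
2. Replace the t-test on counts. For each category, compare the number of patients with at least one (serious) adverse event, giving the risk difference with an exact interval and an exact test.
3. Add event rates per patient-year of follow-up, either descriptively or from a Poisson or negative binomial model with log follow-up time as offset.
4. Summarise the delayed arm's months 18-36 descriptively as on-treatment experience, not as the comparator.

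The cost is a change of wording in two sections and minor analysis work. No new data, visits or patients are needed.
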